## IV. **CHOOSING AND EVALUATING A MICRONUTRIENT SUPPLEMENT FOR PREGNANT WOMEN**

There are many opportunities for reducing maternal morbidity and mortality and for improving the nutritional status of the mothers and infants through maternal micronutrient supplementation. The most important micronutrients seem to be iron, folate and vitamin A/ $\beta$ -carotene, while other micronutrients such as zinc also play an important role. Therefore, a multiple vitamin/mineral supplement is indicated. The question about the impact of individual micronutrients is mainly of scientific interest, and has limited relevance for a population with a generally poor quality diet. Moreover, the additional costs of adding a few more micronutrients to an existing pre-natal supplement (e.g.

iron/folate) is marginal, and would provide women with better access to a broader range of essential micronutrients.

A recent meta-analysis of studies that compared weekly to daily iron supplementation concluded that supplementation should be continued on a daily basis. In the NNIPS-2 trial, the vitamin A/ $\beta$ -carotene supplements were provided on a weekly basis. However, because a multi-micronutrient supplement for pregnant women should contain iron/folate, which must be taken on a daily basis, a daily supplementation schedule is also proposed for the SUMMIT intervention. The proposed multi-micronutrient supplement has recently been adopted by UNICEF following the July 1999 UNICEF/WHO/UNU Workshop, "Composition of a Multi-micronutrient Supplement to be Used in Pilot Programs Among Pregnant Women in Developing Countries." This supplement is intended for use in effectiveness trials in pilot countries, and meets the recommended daily allowances for pregnancy of the United States and Canada. The composition of the SUMMIT supplement and a summary of the workshop proceedings are included in Appendix 3. Although calcium and magnesium are absent from the supplement, this reflects the practical consideration of having supplements sufficiently small to be easily swallowed rather than any perceived lack of importance of these nutrients. Future interventions may also evaluate the impact of calcium and magnesium on pregnancy-related morbidity and mortality.

Current practice in Indonesia is for pregnant women to receive at least 90 tablets containing 60 mg iron and 250  $\mu$ g folate to be taken on a daily basis as part of routine antenatal care. For the SUMMIT activity distribution of tablets will be more frequent with participants receiving tablets daily from the first antenatal clinic attendance to 90 days post-partum. The supplements will be either the multi-micronutrient combination or a matching tablet containing 30 mg iron and 400  $\mu$ g folate. This strategy and formulation are proposed to maximize health benefit and compliance, and minimize any side effects. Thus, the intervention will compare the impact of a multi-micronutrient supplement for pregnant women to that of an iron/folate supplement.

## **V. SUPPLEMENT DISTRIBUTION**

We propose to utilize the existing antenatal-care and maternal health information system as the mechanism for distributing the supplements and monitoring simple coverage rates. As mentioned above, supplements will be provided daily from the first prenatal consultation for a confirmed pregnancy through 90 days post-partum. The HKI intervention staff will provide additional detailed monitoring of compliance, and also work with the midwives to increase their knowledge of the importance of maternal nutrition and strengthen their capacity for distribution of supplements, record-keeping and monitoring. To avoid over-consumption of supplements, it will be carefully emphasized to midwives and pregnant women participating in SUMMIT that one tablet is to be taken daily, and that the supplement is in place of, and not in addition to, the normal MOH iron/folate supplement.

Use of the antenatal-care system will not only provide an opportunity for improvement of services in the area where the trial is being conducted, but will also provide valuable lessons learned for national policy and programming. Similarly, improving the existing health information system for impact monitoring will also strengthen the system. Importantly, independent monitoring of the system will be carried out by HKI to assess the reliability of the data obtained and for improving performance where necessary.

Importantly, the SUMMIT activity will not only provide information concerning the impact of micronutrients, but it will also assess the specific impact of activities accompanying the intervention such as promotion of prenatal care and social marketing. Evaluation of the relative individual effects of these factors as opposed to the multi-nutrient supplement itself will provide the basis for a cost-benefit analysis that will help the GOI to make informed decisions regarding health budget allocations. This evaluation will be achieved by first establishing a demographic surveillance system throughout the island so that district-specific maternal and infant mortality rates can be estimated. This will be followed by phased in prenatal care promotion and social marketing, and implementation of multiple micronutrient distribution.

## **VI. OBJECTIVES AND GOALS**

The proposed SUMMIT activity focuses on decreasing maternal and early infant mortality, and increasing birth weight by improving micronutrient status during pregnancy and lactation. This will include activities aimed at increasing demand among mothers for the supplement early in pregnancy through education and social marketing, and careful monitoring of compliance. The activity will, therefore, help to improve the micronutrient status of women during and after pregnancy.

### **A. General objectives/goals**

The primary goals of the SUMMIT activity are to determine if daily multi-micronutrient supplementation among pregnant women will:

- Reduce the frequency of maternal mortality
- Reduce the frequency of low birth weight
- Reduce the infant mortality rate

### **B. Specific objectives**

The specific objectives will be to determine the relative impact of multi-micronutrient and iron/folate supplements on maternal and infant health, by assessing:

- i. Maternal mortality defined as pregnancy-related deaths per 100,000 live births (MMR), and also pregnancy-related deaths per 100,000 pregnancies within 6 weeks of termination of pregnancy (MMRT)
- ii. Birth weight
- iii. Neonatal and infant mortality
- iv. Maternal morbidity (e.g. hemorrhage, prolonged labor)
- v. Maternal micronutrient status

## **VII. PROJECT ACCOMPLISHMENTS TOWARD USAID/I MISSION'S STRATEGIC OBJECTIVES**

The Maternal SUMMIT activity is directly in line with USAID/I Mission's Strategic Objective, "Protecting the Health of the Most Vulnerable Women and Children" during the crisis and recovery period. The activity fully supports USAID/I's "Essential Services Component Two: Maternal and Neonatal Health (MNH)," by working through the existing health care system, to assist in "maintaining and ultimately improving the quality

and delivery of services that have proven effective in addressing the most important causes of maternal and neonatal morbidity and mortality.” The activity contributes directly to the Essential Package of Safe Motherhood Services, which focuses on “improving the clinical skills of midwives for antenatal care; birthing practices for safe delivery; appropriate management of complications, including timely referrals; identification of risk factors for neonatal mortality; care of normal and sick neonate infants; and postpartum care”. It also contributes to strengthening “demand generation and community empowerment efforts to improve birth preparedness,” strengthening “the technical and management capacity” of midwives, and supporting efforts to “improve the utilization of safe motherhood and child health services at the community level.” The activity also works toward “a decrease in the prevalence of anemia among pregnant women in project areas” (IR1: Essential Services Preserved) and an increase in the “percentage of adults knowledgeable about maternal complications of pregnancy and childbirth” (IR3: Promotion of Appropriate Behaviors and Services).

## Relationship of HKI with other Organizations and the Government of Indonesia

HKI will collaborate with various departments of the Indonesian MOH at the national, provincial and district levels. HKI will continue to work closely with other USAID grantees, cooperating agencies, and contractors of USAID-funded activities in the field of maternal health and antenatal care to reduce micronutrient deficiencies, particularly iron deficiency anemia and vitamin A deficiency. The Turner Foundation (Cable News Network [CNN]) has already provided, through UNICEF, an initial US\$840,000 for the Maternal SUMMIT activity to support the intervention from May 1999 until December 2000.

A Steering Committee and several Advisory Committees have been proposed at the national and local level to facilitate the work (Appendix 4). These are composed of counterparts and donor agency representatives, and includes the following organizations: MOH/Binkesmas/Gizi, MOH/NIHRD, BAPPEDA, DINKES, University of Mataram, USAID, UNICEF, WHO, and HKI.

## **VIII. IMPLEMENTATION**

### **A. Schedule**

The five-year implementation schedule for the trial is broadly described below:

|                |                                                                                                                                                                                                                                                                                                                                                                                                                                                                                                                                                                                       |                           |
|----------------|---------------------------------------------------------------------------------------------------------------------------------------------------------------------------------------------------------------------------------------------------------------------------------------------------------------------------------------------------------------------------------------------------------------------------------------------------------------------------------------------------------------------------------------------------------------------------------------|---------------------------|
| Phase I | Preparatory phase                                                                                                                                                                                                                                                                                                                                                                                                                                                                                                                                                                     | December 1999-August 2000 |
|                | 
In this phase, we will focus on preparations for the trial, including meetings with the appropriate provincial and district level MOH staff, community leaders and midwives. A field office will be established in Mataram, the capital of Lombok. Staff will be hired and trained. Survey protocols, field manuals and data collection forms will be designed and tested, and management systems will be put in place.
 
At the same time efforts to increase community links to the health care system will be conducted by development of appropriate social marketing
 |                           |

campaigns and educational materials to increase awareness within the community and demand for the supplements.

**Phase II**      Supplementation trial      September 2000-September 2003

Implementation of the double blind, community-based, cluster-randomized, controlled trial will start. Pregnant women will be enrolled for follow up over the course of pregnancy and until three months postpartum. Once the target number of pregnancies has been enrolled, enrollment will be discontinued. Women who have not yet delivered their babies will be followed until three months after delivery.

The design, sample size, and methods are detailed below (in Section B. Implementation methods).

**Phase III**      Analysis and Report Preparation      October 2003-October 2004

The study will produce a great deal of data, requiring extensive analysis. Scientific papers, reports and presentations of the findings will be made.

**B.      Implementation methods**

*1.      Study area and population*

The proposed field site is Lombok Island in Nusa Tenggara Province. This site was chosen through a consensus process that evaluated qualitative and quantitative data from districts throughout Indonesia based on demographic and health indicators including maternal and infant mortality rates, nutritional status, total population, population density, health infrastructure, physical infrastructure, and local government support and stability.

Despite many years of program interventions by the GOI and NGOs, NTB remains one of the poorest provinces in the country. The UNDP development index ranked the province of NTB as 26th of 27 provinces, above only East Timor (1993 data). The 1997 IDHS found that in NTB 85% of women deliver their babies at home, with 78% attended by a traditional birth attendant. Although a provincial level maternal mortality ratio (MMR) for Lombok has not yet been established, when compared to the overall rates for Indonesia, infant and under-five mortality rates for NTB are high (see Table 1).

The island of Lombok is home to approximately 2.6 million people, approximately two-thirds of the population of NTB province. The total area of the island is 4,739 km^2, and it is one of the most densely populated areas in Indonesia, with an average of 568 persons per km^2 (population densities by district: West Lombok 416/ km^2; Central Lombok 515/km^2; East Lombok 590/km^2; Kodya Mataram 5,724/km^2). The climate of the island is tropical and wet, with a relatively dry season from May to October and a wet season from November to April. Between these two main seasons are two short transitional periods. Geographically, three zones can be identified, running across the island from the northwest to the southeast: the drier and mountainous North and northwest, which is taken up in large part by the dormant volcano Gunung Rinjani; the Central zone which includes the more wet, fertile and densely populated hills and plains to the south and east of Gunung Rinjani; and the mostly dry and hilly South and Southeast.

The largest city on Lombok is Mataram, the capital of NTB province, with a population of approximately 300,000. West Lombok district consists of 13 sub districts and 99 villages with a population of around 530,000 people. Central Lombok consists of 12 sub districts and 119 villages and has a population of about 750,000 people. East Lombok consists of 16 sub districts and 109 villages with a population of about 1,000,000 people. The trial will be conducted in approximately 300 villages in West, Central and East Lombok Districts. Based on demographic data from the government of NTB and additional data collected from NGOs, we estimate that 72,000 pregnancies will occur annually in the 300 villages.

## 2. *Design and Methods*

The proposed SUMMIT activity is a double blind, community-based, cluster-randomized, controlled intervention designed to assess the relative impact of multi-micronutrient supplements compared to iron/folate supplements on maternal mortality, infant mortality and low birth weight. Pregnant women will be randomized to one of approximately 300 clusters defined by the geographic area serviced by a trained midwife. This means that all women attended by a particular midwife will receive the same type of supplement. Clustered randomization was chosen due to the logistical and scientific difficulties associated with individual randomization in large scale longitudinal trials. Pregnant woman will be provided with either a daily multi-micronutrient supplement containing iron, folate, vitamin A, and zinc, along with additional B vitamins, minerals, anti-oxidants (for precise composition, see Appendix 3a), or an identical-looking daily supplement containing 30 mg iron and 400 µg folate. There will be no blank placebo group because iron/folate supplementation distribution to pregnant women is the current policy of the GOI.

The intervention will be preceded by a 6-month baseline demographic surveillance period to estimate area-specific maternal and infant mortality rates. Supplementation will then be phased in step-wise by implementation in 1/3 of the villages over 3 successive 3-month intervals. Women who refuse to be included in the trial and those in the pre-intervention areas will receive the standard GOI iron/folate tablets. The GOI iron/folate tablets will, therefore, not be withdrawn from the island but will only be used for individuals not enrolled in the intervention portion of the activity.

Supplements will be provided free to all women with a confirmed pregnancy, from the first antenatal consultation up to three months postpartum. As a joint activity between HKI and the GOI, the existing government system will distribute the supplements to pregnant women and the government-trained midwives will be involved in monitoring the health impact. HKI project staff will also encourage the midwives to provide maximum supplementation coverage. Additional non-invasive surveillance will be carried out by HKI project staff to allow adequate assessment of compliance and health impact.

## 3. *Sample Size*

The sample size is influenced by the minimal desirable detectable effect of the intervention, the event rate of the outcome, and the duration of the intervention. The desired detectable effect is influenced by the magnitude of the plausible effect size and the importance of the preventable event. Initial estimates of a plausible effect size of multi-micronutrient supplementation on maternal mortality can be guided by childhood

mortality-related effects observed for other micronutrients such as vitamin A and iodine, which range from 20-70%. While acknowledging that physiological differences between children and pregnant women limit the utility of such information, additional perspective is gained from the results of the NNIPS-2 study which described a vitamin A-mediated 40% reduction in mortality related to pregnancy. Given the relatively low-cost of a prenatal nutrient-based intervention, the documentation of a 20-30% effect, especially under programmatic settings, would be important. The estimates of the maternal mortality ratio in various districts on Lombok range from 400 to 800 maternal deaths per 100,000 live births. For this intervention the unit of randomization will not be the individual woman, but the area or cluster of communities administered by the midwife. This improves logistical feasibility but reduces statistical power due to the potentially correlated outcomes within each cluster. Given the estimated between-cluster variability in MMR, we have calculated that a 20% increase in sample size is needed to compensate for the loss of statistical power from the cluster-based randomization. We further anticipate a loss to follow-up of approximately 10%. Lastly, because not all pregnancies result in a live birth, it is estimated that the required sample size be increased an additional 15% to compensate for abortions, miscarriage, and stillbirths. Given these factors, the sample size table below presents the number of pregnancies required to obtain significance for various observed reductions in MMR for the proposed 2-arm design.

| Detectable
reduction
(%) | Total pregnancies needed by baseline MMR
(deaths/100,000 live births) |                |                |
|-----------------------------------------|----------------------------------------------------------------------------------|----------------|----------------|
|                                         | MMR=400                                                                   | MMR=600 | MMR=800 |
| 15                                      | 509,635                                                                          | 339,137        | 253,887        |
| 20                                      | 281,023                                                                          | 187,017        | 140,012        |
| 25                                      | 176,230                                                                          | 117,290        | 87,815         |
| 30                                      | 119,865                                                                          | 79,777         | 59,731         |
| 35                                      | 86,232                                                                           | 57,381         | 42,967         |
| 40                                      | 64,581                                                                           | 43,035         | 32,192         |

Assuming a conservative MMR estimate of 400 per 100,000 live births, enrollment of 120,000 pregnancies will allow determination of a reduction in MMR of at least 30% with a power of 80% and significance level of 0.05. Similar reductions in MMRT will also be detectable because such rates are expected to be higher given that deaths prior to a live-birth delivery would be included. Given the estimated 72,000 pregnancies per year in the 300 villages on Lombok, and taking into account the phased in implementation schedule, the SUMMIT activity will plan to enroll 126,000 pregnancies over a 2 year active recruitment period. If MMR and MMRT approach 600-800 per 100,000 live births or pregnancies, which is possible considering the high rates of infant and under-five mortality, the sample size of 126,000 pregnancies will allow determination of a statistically significant reduction in MMR and also MMRT of 22-25%.

For infant mortality it will be important to also determine the age-specific effects on neonatal mortality rate (NMR, birth to 30 day mortality) and post-neonatal mortality rate

(PNMR, 1 to 12 months). The projected sample size and trial duration will allow detection of at least a 10% change in NMR and PNMR. In addition, the study will easily detect a difference of 10% in the proportion of low-birth weight (LBW) infants.

| Detectable
reduction
(%) | Total live births (LB) needed |                        |                      |
|-----------------------------------------|--------------------------------------|------------------------|----------------------|
|                                         | NMR=46/1000 LB                | PNMR=64/1000 LB | LBW=15/100 LB |
| 10                                      | 83,012                               | 58,613                 | 22,862               |
| 15                                      | 36,231                               | 25,597                 | 10,016               |
| 20                                      | 20,006                               | 14,142                 | 5,552                |
| 25                                      | 12,561                               | 8,899                  | 3,498                |

As is general practice for community-based trials, a Data Safety and Monitoring Committee will be convened, and trial data will be evaluated after two years. Should documentable reductions be likely, the committee will decide whether the trial should be terminated or extended. For example, if a 20% reduction in MMR is observed in the multi-nutrient group compared to a MMR of 600/100,000 live births in the iron/folate arm, an approximate 6-month extension would be needed to demonstrate statistical significance.

Sample size determinations are needed for the evaluation of the impact of activities, such as promotion of prenatal care and nutrition, accompanying the supplement distribution. Through the baseline demographic surveillance and continued monitoring of maternal and infant mortality as the intervention is phased in, we propose to document the effect of the activities associated with program implementation on maternal and infant mortality. This will be estimated by comparing MMR, MMRT, and IMR between the non-intervention areas and the iron/folate arm of the intervention area. For the non-intervention area we estimate that maternal and infant mortality rates will be estimated for 54,000 pregnancies. This will be compared to the rate obtained for the iron/folate arm of the intervention for 63,000 pregnancies. This will enable detection of at least a 20-25% (power=80% with  $p<0.05$ ) effect of the program implementation, independent of the multi-micronutrient impact.

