*Sample Size:* The SUMMIT activity will aim to detect a reduction in both MMR and MMRT of at least 30% with a power of 80% and significance level of 0.05. Current estimates of the MMR in various districts on Lombok range from 400 to 800 maternal deaths per 100,000 live births and randomization for the trial will be by clusters consisting of geographic areas serviced by each of the 300 midwives providing prenatal care. Assuming 400 maternal deaths per 100,000 live births and a 10% loss to follow-up, the trial would require enrollment of 102,000 live birth pregnancies allocated to either an iron/folate or multinutrient supplement to detect a 30% reduction in MMR. Because not all pregnancies result in a live birth, it is estimated that the required sample size be increased an additional 15% to 120,000. This sample size will also allow detection of similar reductions in MMRT. It is proposed that enrollment be phased in over a 6-month period and continue for at least 2 years to accommodate seasonal effects. The phased in implementation along with the approximately 72,000 pregnancies occurring each year throughout the trial area yields a projected enrollment of 126,000 pregnancies. The additional margin of enrollment provides the ability to detect reductions in MMR as little as 22% if ratios approach 800 per 100,000 live births. With regard to low birth weight and infant mortality rates, the projected sample size will allow detection of at least a 10% reduction in low birth weight and infant mortality rates, including neonatal mortality rates. Equally important is determination of the impact of the social marketing and education programs that will accompany the trial implementation in the intervention area. Data concerning outcome variables in the absence of the intervention will be collected during the phase-in period prior to enrollment. This will result in the ability to detect at least a 25% difference in MMR between the iron/folate arm of the intervention area compared non-intervention areas.

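### The maternal mortality sample-size table under-inflates the 10% loss and applies one design effect of 1.2 to every cell although about 300 clusters are fixed, so its cells cannot all be right; the main target still stands

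*Protocol*

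**What the plan says.** Protocol section VIII.B.3 (Sample Size) lists three inflations: for clustering, "we have calculated that a 20% increase in sample size is needed"; for attrition, "We further anticipate a loss to follow-up of approximately 10"%; and a further 15% for pregnancies that do not end in a live birth. The MMR table then gives 18 totals, for reductions of 15% to 40% at MMR 400, 600 and 800.

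The headline reading is that "enrollment of 120,000 pregnancies will allow determination of a reduction in MMR of at least 30% with a power of 80"%. The plan is to enrol 126,000, and the text adds that this size detects reductions of 22–25% if MMR is 600–800.

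Section VIII.B.2 sets the units of randomization: "approximately 300 clusters defined by the geographic area serviced by a trained midwife".

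For the data monitoring committee, section VIII.B.3 gives an example of a 20% reduction against MMR 600 in the iron/folate arm, for which "an approximate 6-month extension would be needed to demonstrate statistical significance".

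Section VIII.B.6 says the design effect will be assessed from the baseline demographic surveillance.

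**The concern.** If 10% of women are lost, the number to enrol is the number needed divided by 0.90. Multiplying by 1.10 covers a loss of only 9.1%. The table treats its two kinds of attrition differently, because non-live births are divided by 0.85.

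The design effect matters more. With cluster size m and ICC ρ it is 1 + (m − 1)ρ. The number of midwife areas does not change, so a larger total means larger clusters and a larger design effect. A flat 1.2 can be right for at most one cluster size. Beyond that size, adding women to the same areas buys less than the table says; below it, the table asks for too many.

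At stake are the credibility of the table, the 22–25% statement at MMR 600–800, and the extension example. Section VIII.B.3 itself calls a 20–30% effect important, so the 20% rows matter.

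**Working it through.** **Inputs.** Section VIII.B.3: α 0.05 (sidedness is not stated; two-sided fits the table), power 80%, design effect 1.2, loss 10%, non-live births 15%, 72,000 pregnancies per year, planned 126,000. Section VIII.B.2: about 300 clusters, two arms.

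**Step 1: reproduce the stated figure.** For 0.004 against 0.0028, the continuity-corrected two-proportion size over both arms is 77,172.
- 77,172 × 1.2 × 1.10 = 101,867 live-birth pregnancies (Executive Summary: 102,000).
- 101,867 / 0.85 = 119,844 (table: 119,865).
- All 18 cells agree with this recipe within 0.13%. The ratio of stated to unadjusted size is 1.553–1.555, against 1.2 × 1.10 / 0.85 = 1.553. With loss as /0.90 it would be 1.569, which fits less well.

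**Step 2: correct the loss.** 77,172 × 1.2 / 0.90 / 0.85 = 121,054, or 1.0% more. With loss as /0.90, power by the protocol's own method is 79.6% at 120,000 and 81.6% at 126,000. Without the continuity correction it is 81.4% and 83.2%.

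**Step 3: test the flat design effect.** Followed live births per cluster are N × 0.90 × 0.85 / 300 = N × 0.765 / 300.
- Smallest cell: 32,192 × 0.765 / 300 = 82. A design effect of 1.2 implies ρ = 0.2 / 81 = 0.0025.
- Largest cell: 509,635 × 0.765 / 300 = 1,300. A design effect of 1.2 implies ρ = 0.2 / 1,299 = 0.00015.

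The two differ about 16-fold, so no single non-zero ICC fits both ends. A constant between-cluster coefficient of variation (CV) would make the design effect nearly equal across a row of the table, but it would still change from row to row.

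**Step 4: recompute with 300 clusters.** Let N₀ be the unadjusted live births. The analysed number n solves n = N₀[1 + (n/300 − 1)ρ], so n = N₀(1 − ρ) / (1 − N₀ρ/300), and pregnancies = n / 0.765. The protocol does not say where 1.2 was calibrated, so two cases are shown.
- Set at 119,865: m = 305.7, ρ = 0.2 / 304.7 = 0.000656, CV = √(0.000656 × 0.996 / 0.004) = 0.404.
- Set at 509,635: m = 1,299.6, ρ = 0.000154.

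Example, 20% at MMR 400 with 1.2 set at 119,865: N₀ = 281,023 / 1.5532 ≈ 180,930; N₀ρ/300 = 0.396; n ≈ 299,300; pregnancies ≈ 391,000.

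| Reduction, MMR | Stated | 1.2 set at 119,865, constant ICC | 1.2 set at 119,865, constant CV | 1.2 set at 509,635, constant ICC |
|---|---|---|---|---|
| 30%, 400 | 119,865 | 121,296 | 121,296 | 105,024 |
| 25%, 400 | 176,230 | 197,179 | 197,179 | 157,469 |
| 20%, 400 | 281,023 | 391,258 | 391,258 | 260,685 |
| 20%, 600 | 187,017 | 213,559 | 260,335 | 167,738 |
| 25%, 600 | 117,290 | 118,174 | 131,199 | 102,676 |

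A 22% reduction at MMR 800 has no table cell. With 1.2 set at 119,865 it needs about 115,000 under a constant ICC and about 143,000 under a constant CV.

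**Step 5: power at 126,000 for the 22–25% statement** (1.2 set at 119,865, continuity-corrected, loss as /0.90). For 25% at MMR 600: 82.1% under a constant ICC, 78.7% under a constant CV. For 22% at MMR 800: 82.9% and 76.4%.

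**Step 6: the extension example** (20% at MMR 600).
- Read as 80% power, the protocol's own cell gives (187,017 − 126,000) / 72,000 = 0.85 years, about 10 months.
- Read as significance of an observed 20% reduction, with 126,000 enrolled, loss as /0.90 and design effect 1.2, each arm has 126,000 × 0.765 / 2 / 1.2 = 40,163 effective live births. Then z = 0.0012 / √(2 × 0.0054 × 0.9946 / 40,163) = 2.32, which is already significant.

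Six months matches neither reading.

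**The case against.** Four objections deserve weight.

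- **The loss error is tiny.** The protocol says approximately 10%, the change is 1%, and the trial plans 126,000. This stands. A reader might infer from 79.6% at 120,000 that the trial is underpowered; the documents do not support that, since 126,000 gives 81.6%.
- **The size of the design-effect error rests on an unstated calibration point.** This stands. It is tempting to say that the large cells are badly understated, but that holds only if 1.2 was set near 120,000. For 20% at MMR 600 under a constant ICC, the requirement runs from about 168,000 to 213,600 depending on that choice. What the objection does not remove is that the cells are mutually inconsistent whichever point is chosen.
- **The extension contrast cannot be blamed on the design effect.** Recomputed cells of 213,559 and 260,335 would imply about 15 and 22 months beyond 126,000, and a reader might set those against the stated six. But the protocol's own cell already implies 10, and the sentence speaks of significance rather than power. The example is unreliable for its own reasons. The protocol also does not say that the committee would read its decision from the large cells.
- **The design effect is to be assessed at baseline** (section VIII.B.6). This shows that 1.2 is provisional, but it corrects neither the printed table nor the example given to the committee.

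**Conclusion.** The point holds in a limited form. The MMR table under-inflates loss and uses one design effect that cannot apply to all of its cells.

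The main target stands: 30% at MMR 400 needs about 121,000, and the planned 126,000 gives about 82% power. This rests on two-sided testing with continuity correction, which is how the table was built, and on the protocol's 1.2 applying near the planned size.

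The wider effect is conditional. If 1.2 was calibrated near 120,000, the 20% cells at MMR 400 and 600 are too small by about 39% and 14% under a constant ICC (391,258 / 281,023 and 213,559 / 187,017). A constant CV makes the latter 39% (260,335 / 187,017), and the 22–25% statement at MMR 600–800 then needs about 131,000 to 143,000, more than planned. If 1.2 was calibrated at the largest cell, the large cells are about right or conservative and the headline 120,000 is more than needed.

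The ICC and CV used here are back-calculated from the 1.2 at the assumed cell; the protocol gives neither.

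**What to change.** 1. State the ICC or coefficient of variation behind the 20%, and the cluster size for which it was calculated.
2. Recompute each MMR cell with 300 clusters, a design effect of 1 + (m − 1) × ICC for that cell's own cluster size, and loss as /0.90. If between-cluster variation is taken as proportional to the rate, use a constant CV across the MMR columns. Update the table when the baseline design effect in section VIII.B.6 is available.
3. Restate the headline: about 121,000 pregnancies for 30% at MMR 400, and about 82% power at 126,000. Restate the 22–25% claim at MMR 600–800 under the declared assumption.
4. Recompute the extension example, and say whether it means 80% power or significance of an observed 20% reduction.

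Cost: slightly less favourable stated figures and a short recalculation. No extra participants are needed, because the planned 126,000 still covers the main target.
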